### Methodological endpoint: use of ePROM (electronic patient-reported outcome measures)

At the suggestion of patients involved in trial design, measures of pain and oral function and analgesia use are recorded every 15 days using a bespoke smartphone application. This data is entered by patients remotely upon receiving a notification, and data is subsequently populated directly to the RAPTOR trial database. A further secondary endpoint analysed will thus be the degree of completeness of data recorded using this ePROM. For patients without access to smartphones, alternative methods using computer website or telephone-based questionnaires are provided.

### Participant timeline {13}

The schedule of enrolment. Interventions, assessments and visits are illustrated in Fig. 2 and Table 3.

**Fig. 2 Fig2:**
[figure not shown]
Trial schema RAPTOR trial

**Table 3 Tab3:** Participant timeline RAPTOR trial

Assessment	Screening	Baseline^a^	Randomisation	2-week check by telephone	Clinic visit schedule *(in months)*				*Optional clinic visits*^b^ *(in months)*							Study completion^b^
					**3**	**6**	**9**	**12**	**15**	**18**	**21**	**24**	**27**	**30**	**33**	
Clinic visit numbers					1	2	3	4	5	6	7	8	9	10	11	
*Accepted Variance*				± *1 week*	± *1 month*											± *1 months*
Informed consent	X															
Assessment of eligibility criteria	X															
Confirmation of eligibility	X															
Review of medical history	X	X														
Review of concomitant medications (including analgesia and antibiotic usage)	X	X			X	X	X	X	X	X	X	X	X	X	X	X
Demographics^c^	X															
General oral/head and neck examination	X	X			X	X	X	X	X	X	X	X	X	X	X	X
Intra-oral examination and assessment of ORN by Notani and CTCAE grade	X	X			X	X	X	X	X	X	X	X	X	X	X	X
ECG^d^	X				X	X		X		X		X		X		X
FBC^d^	X				X	X		X		X		X		X		X
PT and APTT^d^	X				X	X		X		X		X		X		X
UE^d^	X				X	X		X		X		X		X		X
LFT^d^	X				X	X		X		X		X		X		X
Calcium^d^	X				X	X		X		X		X		X		X
Research blood sample	X															
FSH^e^	X															
Pregnancy test^f^	X				X	X	X	X	X	X	X	X	X	X	X	X
Radiology: orthopantomogram	X							X^g^								X^h^
Patient completes training for 15-day return of ePROM^i^		X														
Height and weight measurement and BMI calculation		X			X	X	X	X	X	X	X	X	X	X	X	X
Special assay: clinical photograph with in-field ruler		X						X								X
PROM: EORTC QLQ-30 and H&N35		X			X	X	X	X	X	X	X	X	X	X	X	X
Randomisation			X													
Dispense study medication			X		X	X	X	X	X	X	X	X	X	X	X	
Collection of adverse events		X	X	X	X	X	X	X	X	X	X	X	X	X	X	X

^a^At baseline, all procedures should be done before randomisation

^b^These visits only apply to the patients who chose to continue the study after 12 months. For the rest of the patients, 12 months will be considered as study completion

^c^Gender, ethnicity

^d^During the follow-up period, these tests should be done for patients in Arm B only. During the screening, it should be done for all patients regardless of the trial arm

^e^All women other than those who have had hysterectomy and bilateral oophorectomy

^f^Women with FSH within reference range need pregnancy blood test during the screening. Patients in Arm B need to be tested throughout the treatment period

^g^May use OPT if taken for other clinical reason and within 4 months of study visit

^h^Only repeat OPT at completion if there is more than 4 months after the last OPT

^i^ePROM to be completed every 15 days (or facilitated using website/research staff every 30 days)

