#### Eligibility criteria {10}

Patients must have had prior radiotherapy to the mandible, have diagnosed ORN of the mandible and be considered suitable for medical management. A detailed list of exclusion criteria is given in Table 1. Although definitions of ORN differ, for the purposes of the RAPTOR trial, eligible patients must have exposed mandibular bone either intra- or extra-orally. ORN is classified on clinical and radiographic grounds, from an orthopantomogram (OPT) using a modified version of the Notani Classification [1, 18], and this eligibility and classification of ORN for RAPTOR trial purposes is explained in Fig. 1. Notani class 3 cases are excluded if they have a pathological fracture on clinical assessment, including radiograph, but otherwise may be included. Patients with minor bone spicules (< 20mm^2^) within 12 months of dental extraction/surgery are very likely to heal spontaneously and thus are excluded from the RAPTOR trial. If ORN occurs spontaneously, then patients may be eligible irrespective of the surface area measurements of exposed bone.

**Table 1 Tab1:** Detailed exclusion criteria RAPTOR trial

1. Cannot swallow tablets
2. Prior treatment with PENTOCLO or any element thereof within 12 months of the date of randomisation (4 months, if the PENTCLO is given for ORN prophylaxis reasons at time of dental extractions)
3. Very early ORN after surgery, defined as <20 mm^2^ exposed bone occurring within 12 months of a dental extraction or other dentoalveolar operation
4. Mandibular pathological fracture secondary to ORN
5. Mandibular pathological fracture secondary to ORN
6. Patient has had definitive resection/reconstruction for mandibular ORN—i.e. no longer has exposed necrotic bone present
7. Pregnancy
8. Lactation
9. Age <18 years
10. Acute infection at site of the necrotic bone
11. Hypersensitivity to other methylxanthines
12. Hypocalcaemia
13. Participants not willing to follow the contraceptive requirements of the protocol
14. Contraindications to PENTOCLO medications:
a. Known hypersensitivity, allergy or anaphylaxis to pentoxifylline, tocopherol or sodium clodronate
b. Treated hypotension
c. Severe coronary artery disease, defined as grade IV of the Canadian Cardiology Society Angina Grading
d. Severe cardiac arrythmia, defined as those cases with attributable syncope or heart failure associated; or those with frequent and symptomatic palpitations, breathlessness, dizziness, chest pain, weakness or fatigue.

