#### Arm B (intervention arm, PENTOCLO)

Arm B (intervention arm, PENTOCLO) includes the components of SSC as described above *and*: Pentoxifylline 800 mg daily, Tocopherol 1000 mg daily, Clodronate 1600 mg days 1–5 of 7 (Monday through Friday only).

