### Strategies to improve adherence to interventions {11c}

Patient symptoms are collected using a smartphone application (ePROM) as below, which may act as a prompt to improve compliance. In arm B, drugs are dispensed at 3-monthly intervals. A telephone check on adherence is carried out at 2 weeks.

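### Table 3 footnote f ties the screening pregnancy test to an in-range FSH, so as written a woman with below-range FSH has no required test before Arm B drugs are dispensed

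*Protocol article*

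**What the plan says.** The relevant rules are in the protocol article, in Table 3 (Participant timeline {13}) and Table 1 (Eligibility criteria {10}).

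- **Who has FSH measured.** Table 3 schedules FSH at screening. Footnote e defines the group: "All women other than those who have had hysterectomy and bilateral oophorectomy".
- **Who has a pregnancy test at screening.** The pregnancy-test row is marked at screening and qualified by footnote f: "Women with FSH within reference range need pregnancy blood test during the screening". The article gives no other condition for this test and does not define the reference range.
- **Later testing.** Footnote f continues: "Patients in Arm B need to be tested throughout the treatment period". After screening, the next mark in the row is at the 3-month visit, which has a window of ±1 month.
- **Dispensing.** Table 3 marks study medication as dispensed at randomisation and then at each 3-monthly visit. Strategies to improve adherence {11c} agrees: "In arm B, drugs are dispensed at 3-monthly intervals".
- **Eligibility.** Pregnancy is exclusion 7. The only age limit among the exclusions is "9. Age <18 years". Exclusion 13 covers "Participants not willing to follow the contraceptive requirements of the protocol".

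**The concern.** Footnote e has already set aside the surgically sterile women. The job left for FSH is to separate postmenopausal women, who need no pregnancy test, from everyone else. Menopause raises FSH. That is general physiology rather than something the article states, but the rule makes little sense without it. The exemption should therefore depend on one side of the range only: a raised value exempts, and any other value leads to a test.

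Footnote f uses both sides of the range. A low FSH is outside the range just as a high one is, so a woman with a low value falls outside the rule even though nothing shows that she cannot be pregnant.

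What is at stake is participant safety. Exclusion 7 works only if a pregnancy is known. If the rule is followed as written, a woman with low FSH and an unrecognised pregnancy could be randomised untested and, in Arm B, start three drugs that the trial withholds from pregnant women.

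**Working it through.** The article states no figure on this point, so the check is a reading of the rules side by side.

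**Step 1. Possible FSH results under footnotes e and f, for a woman who is not surgically sterile**

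| FSH result | What footnote f requires at screening | What the purpose of the rule requires |
|---|---|---|
| Above range | No test stated | No test (presumed postmenopausal) |
| Within range | Pregnancy blood test | Test |
| Below range | No test stated | Test |

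The two columns differ only in the last row.

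**Step 2. Does the undefined range rescue the rule?** If the range meant is the premenopausal one, the table above applies. If it is the postmenopausal one, footnote f would test postmenopausal women and pass over those below that range, which is worse. Neither reading covers low values.

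**Step 3. Does another stated step catch the case?**

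- Exclusion 7 bars pregnancy but does not detect it.
- Review of medical history and confirmation of eligibility rely on what the woman already knows.
- Exclusion 13 concerns willingness to use contraception and does not show that a woman is not pregnant at entry.
- Table 3 has no pregnancy test at baseline, at randomisation or at 2 weeks.
- At 2 weeks the article plans this: "A telephone check on adherence is carried out at 2 weeks". Gastrointestinal tolerability is also graded then (Table 2). Neither is a pregnancy check.
- The smartphone questionnaire every 15 days covers pain, eating, mouth opening, teeth and gums, painkillers and interference with daily life (Table 2, item 10). It does not ask about pregnancy.

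**Step 4. Interval in Arm B.** Drugs are dispensed at randomisation. The next pregnancy test is at 3 ± 1 months, so 2 to 4 months after dispensing begins.

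**Step 5. How many women depend on the rule at all?** The article gives no sex or age breakdown, so this rests wholly on assumptions. Take 20 to 40% of the 120 patients as women, and 5 to 20% of those as premenopausal:

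- low end: 120 × 0.20 × 0.05 = 1.2
- high end: 120 × 0.40 × 0.20 = 9.6

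With 1:1 allocation, half of these are in Arm B: 0.6 to 4.8. This counts women for whom the rule has to work. Those with below-range FSH are a subset, and those who also have an unrecognised pregnancy are a small fraction again.

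**The case against.** The strongest objection is that this is one line of shorthand in a condensed article. The article repeatedly refers to a full protocol that is not shown, and exclusion 13 places the contraceptive requirements there. The definition of childbearing potential and the FSH range to apply may well be there too. In addition, footnote f does not contain the word only, and a sensible site would probably read it as meaning FSH that is not raised.

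Part of this stands. The intent was probably to test every woman not shown to be menopausal, and the full protocol may say so. The objection does not remove the point, because the article did not leave the matter to the protocol. It states an operative rule, that rule is the only screening trigger given, and followed literally it misses a group that it exists to cover.

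A reader might also draw stronger conclusions that the document does not support:

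- **That the trial is in fact leaving women untested.** The article shows what the footnote says, not what the full protocol says or what sites do.
- **That pregnant women will typically have low FSH and so slip through.** Nothing in the article addresses this, and it would need an outside source. The gap is shown as a matter of logic, without any estimate of how often it would matter.
- **That an Arm B participant has no contact with the trial before month 3.** She has the 2-week call and the 15-day questionnaire. What is missing is a pregnancy test.
- **That the amount of drug taken in the interval is known to be harmful.** The article gives no safety threshold for use in pregnancy, so a cumulative dose would add apparent precision and no evidence.

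**Conclusion.** The point holds as a minor safety wording error. Footnote f, as written, requires no screening pregnancy test for a woman who is not surgically sterile and has below-range FSH. No other step in the article would detect an unrecognised pregnancy in her before Arm B drugs are dispensed, and her next scheduled test comes at month 3 (±1 month).

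The likely number affected is very small. Under the labelled assumptions about 1 to 10 women depend on the rule, and far fewer, quite possibly none, would be missed. The conclusion rests on a literal reading of the footnote, on the general fact that menopause raises FSH, and on the article alone. It has no bearing on the primary analysis, the error rates or the sample size.

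**What to change.** Check the full protocol first. If it already requires a test for every woman not shown to be postmenopausal, correct only the article's footnote. If it repeats the in-range condition, amend it and tell the sites, since the article reports the trial as open and recruiting.

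Suggested wording for footnote f, first sentence: *Every woman who is not surgically sterile (footnote e) and whose FSH is not in the postmenopausal (raised) range has a pregnancy blood test at screening, with the result available before randomisation.* The second sentence, on testing in Arm B during treatment, can stay.

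The cost is one reworded sentence and a pregnancy assay for each woman with below-range FSH. Under the assumptions above that is fewer than about 10 in the whole trial. Women with raised FSH and surgically sterile women have nothing added, and no visit, analysis or sample-size figure changes.

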### Sample size {14}

Literature-based estimates of the use of PENTOCLO give a 12-month healing rate of approximately 60% and it is considered that this would have to demonstrate an improvement over a 40% rate in the control arm (equivalent to a hazard ratio of 0.56). Using a one-sided alpha level of 0.1 and a power of 90%, then a total of 78 events are required. Including a 5% rate for patient attrition and based on estimated recruitment rates, it is anticipated that 120 patients are required to obtain the events required.

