### Outcomes {12}

The primary outcome measure is time from randomisation to healing of ORN (without the need for surgery), as measured by:Clinical examination by confirming completely healed oral mucosaIntra-oral clinical photographsRadiographs

Conversely, patients who demonstrate failure of treatment as below will be treated as censored observations:Deterioration of ORN including fractureA clinical indication to intervene with mandibular resection and reconstruction

Thus, either the diagnosis of complete healing at 12 months or mandibular fracture or other clinical indication to progress to surgery within 12 months both constitute a primary endpoint for that patient. Other patients whose ORN persists without the need for surgery will also reach the primary endpoint at 12 months, and any change in grade of ORN will be recorded as a secondary endpoint (as below Table 2).

**Table 2 Tab2:** Secondary outcome measures RAPTOR trial

Objectives	Outcome measures	Time point(s) of evaluation
Efficacy:		
1. Deterioration of ORN	Time from randomisation to worsening of ORN as measured: • Extent of exposed bone measured in two dimensions as mm^2^ (and for some trial visits supported by clinical photograph with in-field ruler) and • Notani grade	Every 3 months following randomisation until end of trial for that patient
2. Patients’ analgesia and antibiotic use	• Drug and dose taken for pain relief in the 24-h period leading up to appointment • Days of antibiotic usage. Systemic antibiotics taken since last trial appointment (type, dose and number of days for each type)	Every 3 months following randomisation until end of trial for that patient
3. Patients’ anthropological measurements	Patient BMI (kg/m^2^) where kg is a patient weight in kilograms and m^2^ is their height in metres squared	Every 3 months following randomisation until end of trial for that patient
4. Severity of disease	Grade by “Osteonecrosis of jaw” within CTCAE v 5.0 2017	Every 3 months following randomisation until end of trial for that patient
5. Quality of life	Quality of Life (EORTC QLQ-C30 and QLQ-H&N35)	Every 3 months following randomisation until end of trial for that patient
6. Mandibular preservation	Mandibular preservation rate measured as the removal of mandibula following surgery (segmental resection, with or without reconstruction)	Every 3 months following randomisation until end of trial for that patient
Toxicity:		

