7. Gastrointestinal tolerability of PENTOCLO regimen 2 weeks after commencing (Only in Arm B: PENTOCLO)	Gastrointestinal tolerability, as defined by CTCAE grading	2 weeks after commencing trial medications ± 5 working days, (may be by telephone)
8. Compliance	Evaluation of compliance to the IMP	Every 3 months following randomisation until the end of trial for that patient
9. Assessment of IMP’s combination safety	Evaluation of severe adverse events (severe AEs) and/or serious adverse events (SAEs) considered related to the study treatment	Every 3 months following randomisation until the end of trial for that patient
Exploratory:		
10. Patients’ pain and mouth function	• Pain • Eating • Mouth opening • Problems with teeth/gum • Painkillers used • Interference of these symptoms with patients’ daily activities	Every 15 days until end of trial (for that patient) Collected remotely on smartphone App

To avoid any potential risk of bias due to unblinded site investigators, OPT and clinical photographs taken with an in-field ruler (Puritan stick) are subject to a central blinded review. Training of site investigators is provided during site initiation visits and updates. In cases of trismus, clinical photographs are facilitated by intra-oral cameras which are available with disposable single use covers. Digital copies of the clinical photographs (with in-field rulers) are securely uploaded to the study database by the site staff. At the end of the trial, the central review panel will be provided with the anonymised clinical photographs by the Liverpool Clinical Trials Centre (LCTC) from baseline and 12 months (and at study completion for patients who continue beyond 12 months) for blinded assessment. The outcomes within the patient preference arm of the trial (i.e. after 12 months) will be considered and presented separately. Quality control of images and radiographs from each site is performed from the first images returned and a random sample thereafter.

The secondary outcomes measures include the determination of the impact of PENTOCLO on the deterioration of ORN, analgesia and antibiotic usage, quality of life (using EORTC QLQ-30), mandibular preservation, anthropological measurements, safety, tolerability and compliance of trial medications (complete list Table 2).

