## Statistical methods

### Statistical methods for primary and secondary outcomes {20a}

The primary outcome is time to healing. Healing rates will be estimated using the method of Kaplan and Meier. Comparisons across treatment groups will be performed using a log-rank test. Further analysis adjusting for key demographic and clinical covariates will be performed using a Cox proportional hazards model. The primary analysis will be carried out on the full analysis set, which will be defined on the intention to treat principle, retaining patients in their initially randomised groups irrespective of any protocol violations. Analysis of the primary outcome will be assessed using 1-tailed 0.1 level, as is consistent with the type I alpha level used in the study design. The one-sided test is employed in order to limit sample size and in the light of previous systematic reviews where no detriment to healing from PENTOCLO has been reported. All analyses of secondary outcomes will use the nominal *p* < 0.05 level to determine statistical significance. Full details of all planned analyses will be specified in a statistical analysis plan, which is provided as Appendix 1 (supplementary data).

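### With the primary comparison closed at 12 months, 120 patients are expected to give about 57–60 healing events, not 78, so power is about 82–84% rather than 90%

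*Protocol article*

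**What the plan says.** Sample size {14} of the protocol article takes 12-month healing as about 60% with PENTOCLO and 40% in the control arm, and equates this to a hazard ratio of 0.56. It continues: "Using a one-sided alpha level of 0.1 and a power of 90%, then a total of 78 events are required". It then adds 5% attrition, refers to estimated recruitment rates, and concludes that "it is anticipated that 120 patients are required to obtain the events required". Statistical methods {20a} keeps the same test level: "Analysis of the primary outcome will be assessed using 1-tailed 0.1 level". Allocation is 1:1 (Sequence generation {16a}).

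Outcomes {12} defines the event as healing without surgery. It censors patients who deteriorate, fracture or need resection. For those who neither heal nor need surgery it says: "Other patients whose ORN persists without the need for surgery will also reach the primary endpoint at 12 months". On later data it says: "The outcomes within the patient preference arm of the trial (i.e. after 12 months) will be considered and presented separately". Two other places agree. The patient preference phase (under Intervention description {11a}) lets patients stop or switch arm after 12 months and keeps those data apart from the randomised part. Methods for additional analyses {20b} treats them as non-randomised and mainly descriptive.

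**The concern.** The healing rates behind the hazard ratio are rates at 12 months, and 12 months is also where the randomised comparison ends. The expected number of events therefore follows directly from the planning rates and the patient number, and it falls well short of 78. To reach 78 within 12 months, 65% of 120 patients (or 68% of 114) would have to heal, which is more than the 60% assumed for the better arm.

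What is at stake is how the result is read. The trial is meant to give a first signal of efficacy and to inform a definitive trial. A non-significant result would be judged against a stated 10% risk of missing the planned effect, when on the article's own figures that risk is about 16–18%.

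**Working it through.** **Inputs (Sample size {14} unless stated).** Healing at 12 months 40% and 60%; hazard ratio (HR) 0.56; one-sided alpha 0.1; power 90%; 78 events; 5% attrition; N = 120; 1:1 allocation ({16a}); primary follow-up 12 months and failures censored ({12}).

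**1. Hazard ratio.** Under proportional hazards, ln(1 − 0.40)/ln(1 − 0.60) = 0.5108/0.9163 = 0.5575. This agrees with the stated 0.56.

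**2. Required events (Schoenfeld, 1:1).** Events = 4(z₀.₉₀ + z₀.₉₀)²/(ln HR)², with z₀.₉₀ = 1.2816.
- HR 0.56: 4 × 2.5631²/0.5798² = 78.2
- HR 0.5575: 4 × 2.5631²/0.5843² = 77.0

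The stated 78 reproduces.

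**3. Expected events by 12 months.**
- No attrition: 60 × 0.40 + 60 × 0.60 = 60
- 5% attrition contributing no events: 120 × 0.95 = 114; 57 × 0.40 + 57 × 0.60 = 57
- 5% attrition spread over the 12 months (exponential loss): 58.7

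**4. Power.** Power = Φ(√events/2 × |ln HR| − 1.2816).

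| Events | HR 0.56 | HR 0.5575 |
|---|---|---|
| 57 | Φ(2.189 − 1.282) = 81.8% | 82.2% |
| 60 | Φ(2.246 − 1.282) = 83.2% | 83.7% |
| 78 | Φ(2.560 − 1.282) = 90.0% | 90.3% |

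A simulated log-rank test (exponential healing times, censoring at 12 months, 4,000 runs) gave 82.1% with 114 patients and 83.8% with 120. No run with 114 patients reached 78 events, and about 1 in 4,000 did with 120.

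**5. What would make 120 and 78 fit.** Assume exponential healing at the planning rates.
- Same follow-up for everyone: 78 events need about 20 months with 114 patients, or about 18.5 months with 120.
- Uniform accrual over 18 months, 12 months' minimum follow-up, all followed to study end: the average unhealed proportion is 0.419 (control) and 0.217 (PENTOCLO), so 114 patients give 57 × (0.581 + 0.783) = 77.7 events.

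**6. Effect detectable with 90% power at 12 months.** With control at 40%, solve for the PENTOCLO rate, letting the event count change with it.
- 114 patients: 63.1% (58.8 events, HR 0.512)
- 120 patients: 62.5% (61.5 events, HR 0.520)

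So about 63%.

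**7. Patients needed for 78 events within 12 months.** 78/0.50 = 156 evaluable; 156/0.95 = 164.2, so 165 randomised.

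**The case against.** The strongest defence is the reference to estimated recruitment rates. Recruitment speed affects the event count only when follow-up depends on date of entry, so 120 may have been computed correctly for a design that follows everyone to study end; step 5 shows that such a design can give about 78 events. This stands as a plausible origin, although the article does not state the accrual and follow-up assumptions. A reader should therefore not conclude that someone miscalculated. It does not rescue the stated power, because the article excludes such follow-up from the randomised comparison.

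Outcomes {12} also says that a fracture or an indication for surgery constitutes a primary endpoint for the patient. Counted as events, 18 failures among 120 patients, or 21 among 114, would close the gap. But the same section censors these patients and the outcome is time to healing, so they add nothing to a log-rank test of healing.

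The figure of 57 is the low end. Gradual attrition gives 58.7. The ±1 month visit window in Table 3, if every patient were seen at month 13, gives about 60 events from 114 patients. Combining that with no attrition at all gives about 63 events from 120 and about 85% power. A range is therefore fairer than one figure, but no version approaches 78.

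Other stronger readings are tempting but unsupported:
- That the analysis waits for a trigger of 78 events that never comes: no section describes an event-triggered analysis.
- That censoring failures lowers power further by a known amount: the article gives no planning rate for failures. If 40% and 60% are crude proportions healed, failures already lie in the unhealed fraction.
- That the trial cannot answer its question: a shortfall of 6–8 percentage points does not show that, and neither the type I error nor the treatment estimate is affected.

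**Conclusion.** The point holds as a contradiction between Sample size {14} and the fixed 12-month endpoint in Outcomes {12}, the patient preference phase and {20b}. The 78 events are right for 90% power at HR 0.56; the claim that 120 patients will supply them is not. About 57–60 healing events are expected, giving about 82–84% power.

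This rests on the article's own healing rates, 1:1 allocation, proportional hazards, healing as the only event, and no randomised follow-up beyond 12 months. The range covers 5% attrition with no events from those lost through to no attrition, and the hazard ratio as rounded (0.56) or unrounded (0.5575).

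**What to change.** Reword Sample size {14} to match the 12-month endpoint. For example: with 120 patients, up to 5% attrition and 12 months' follow-up, about 57–60 healing events are expected, giving about 82–84% power at a one-sided 0.1 level to detect 40% against 60% healing (90% power for 40% against about 63%). The 78 events may stay as the number that 90% power at HR 0.56 would require, but should no longer be presented as what 120 patients will deliver. The full protocol and analysis plan should carry the same statement wherever they repeat the present one.

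The cost is wording and a less favourable stated power; no extra patients are needed. If the sponsor prefers to keep 90% power for 40% against 60% with a 12-month endpoint, the price is about 165 randomised patients, 45 more than planned.
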